## 12 END OF TRIAL PARTICIPATION

All participants who enter remission will continue in trial follow up until relapse or trial closure when the total number of primary endpoint events have been observed (refer to section 16.2), whichever occurs first. It is anticipated that the end of trial will be approximately 30 months after the last patient recruited.

Once participants have completed their participation in the trial, they will return to normal standard of care.

### 12.1 Trial Restrictions

Women of childbearing potential are required to use adequate contraception for 12 months after the last dose of rituximab. This includes:

- Intrauterine Device (IUD).
- Hormonal based contraception (pill, contraceptive injection or implant etc.).
- Barrier contraception (condom and occlusive cap e.g. diaphragm or cervical cap with spermicide).
- True abstinence (where this is in accordance with the participant's preferred and usual lifestyle).

## 13 ASSESSMENT OF SAFETY

### 13.1 Definitions

#### 13.1.1 Adverse event (AE)

Any untoward medical occurrence in a participant or clinical trial participant administered a medicinal product and which does not necessarily have a causal relationship with this treatment. An AE can therefore be any unfavorable and unintended sign (including an abnormal laboratory finding), symptom, or disease temporally associated with the use of an IMP, whether or not considered related to the IMP.

Please note: Recording of all SAEs and selected AEs of interest must start from the point of Informed Consent regardless of whether a participant has yet received a medicinal product.

#### 13.1.2 Adverse Reaction (AR) to an IMP

All untoward and unintended responses to an IMP related to any dose administered. All AEs judged by either the reporting investigator or the sponsor as having a reasonable causal relationship to a medicinal product qualify as ARs. The expression reasonable causal relationship means to convey in general that there is evidence or argument to suggest a causal relationship.

#### 13.1.3 Unexpected Adverse Reaction

An AR, the nature, or severity of which is not consistent with the applicable reference safety information (RSI) (e.g. the summary of product characteristics (SmPC) for an authorised product as specified in section 4.8. When the outcome of the AR is not consistent with the applicable RSI this AR should be considered as unexpected.

The term "severe" is often used to describe the intensity (severity) of a specific event. This is not the same as "serious," which is based on participant /event outcome or action criteria.

#### 13.1.4 Serious Adverse Event or Serious Adverse Reaction (SAE / SAR)

Any untoward medical occurrence that at any dose:

- results in death
- is life-threatening
- requires hospitalisation or prolongation of existing inpatients' hospitalization
- results in persistent or significant disability or incapacity
- is a congenital anomaly or birth defect
- is an important medical event - Some medical events may jeopardise the participant or may require an intervention to prevent one of the above characteristics/ consequences. Such events (hereinafter referred to as 'important medical events') should also be considered as 'serious'

Life-threatening in the definition of a SAE or SAR refers to an event in which the participant was at risk of death at the time of event; it does not refer to an event which hypothetically might have caused death if it were more severe.

#### 13.1.5 Suspected Unexpected Serious Adverse Reaction (SUSAR)

A SAR, the nature and severity of which is not consistent with the information set out in the RSI.

#### 13.1.6 Reference Safety Information (RSI)

A list of medical events that defines which reactions are expected for the IMP within a given trial and thus determining which SARs require expedited reporting.

The RSI is contained in a clearly identified section of the SmPC or the Investigator's Brochure (IB).

For this trial the RSI is: Section 4.8 (table 2) of the SmPC for Truxima, updated 09/08/2018 approved by the MHRA for use in this trial.

### **13.2 Expected Adverse Reactions/Serious Adverse Reactions (AR /SARs)**

Detailed information about the established risks of rituximab, including expected adverse reactions (ARs), may be found in the latest MHRA approved version of the RSI as specified in section 13.1.6. Expectedness should relate to IMP and not underlying disease.

If the adverse reaction meets the criteria for seriousness, this must be reported as per section **13.5**

The investigator or delegated members of the trial team will be responsible for detecting, documenting and reporting safety events that meet the definition of an AE/AR or SAE/SAR. Adverse Reactions of Special Interest related to trial treatment (Rituximab):

- Systemic infusion/injection reactions
- Hypogammaglobulinaemia (IgG <400 mg/dL (Grade 3) and <250 mg/dL (Grade 4))
- Hypersensitivity reactions

A number of other adverse reactions of special interest have been identified as being possibly related to the IMP (rituximab) or non-IMP (glucocorticoids or CNIs). – These will be monitored for the duration of the trial. These AERIs are as follows:

- Infections requiring antimicrobial, antiviral or antifungal treatment (including opportunistic, Progressive multifocal leukoencephalopathy )
- Malignancy

### 13.3 Expected Adverse Events/Serious Adverse Events (AE/SAE)

#### *13.3.1 Reporting of expected adverse events*

Due to the underlying clinical condition of the trial population it is not practicable to report all adverse events in this trial and it is thought that excessive safety reporting may detract from the main objectives of the trial. Rather, only AEs of special interest (AESI) should be reported as detailed in section 13.3.

Serious Adverse Events should be reported to the sponsor as detailed in section 13.5.

#### *13.3.2 Laboratory and other safety assessment abnormalities reported as AEs and SAEs*

Abnormal laboratory test results will not be recorded and/or reported as AEs unless they meet the criteria for SAE or AESI. Abnormal laboratory test results should be recorded in the medical notes.

#### *13.3.3 Adverse events of special interest*

A number of adverse events of special interest have been identified as being possibly related to trial treatment (rituximab) and non-IMP (glucocorticoids or CNIs). – These will be monitored for the duration of the trial. These AESIs are as follows:

Related to trial treatment (Rituximab):

- Systemic infusion/injection reactions
- Hypogammaglobulinaemia (IgG <400 mg/dL (Grade 3) and <250 mg/dL (Grade 4))
- Hypersensitivity reactions

Possibly related to the IMP (Rituximab) or non-IMP (glucocorticoids or CNIs):

- Infections requiring antimicrobial, antiviral or antifungal treatment (including opportunistic, Progressive multi-focal leukoencephalopathy)
- Malignancy

Possibly related to non-IMP (glucocorticoids or CNIs):

- New onset Diabetes Mellitus
- Osteoporosis/fracture
- Peptic ulceration/gastritis requiring medication/endoscopy
- Glaucoma
- Cataracts
- Weight gain > 10% (not attributed to oedema)
- Mood changes requiring medication

Hospital admissions – Only those related:

- D1. Hypovolaemia
- D2. Fluid overload secondary to nephrotic syndrome
- D3. Thromboembolic events (due to underlying disease)

Patients with nephrotic syndrome have frequent hospital admissions related to their underlying disease. Hospital admissions related to hypovolaemia or fluid overload secondary to nephrotic syndrome, or to thromboembolic events, will be **exempt from** expedited SAE reporting. However, these events will be designated as Adverse Events of Special Interest and details will be collected in the CRFs.

Each Principal Investigator must report all AESIs to the CI using the CRF in a timely manner. If the AESI is deemed to be serious, then the reporting procedure for an SAE should be followed as detailed in section 13.4, unless the AESI is related to hypovolaemia or fluid overload secondary to nephrotic syndrome.

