#### 11.11 **Relapse Visit**

Patients will be asked to contact their local trial team for review if they have symptoms of relapse including increasing oedema and/or change in proteinuria on dipstick (patients in CR only). Relapse will be confirmed with blood and urine tests, in a trial visit within 2 weeks of indication of relapse. The assessments to be carried out at this visit will be identical to post-remission visit as well as a check for immunoglobulins G and M. However, no further urine dipstick testing will be required.

To help patients identify if they are relapsing, patients in CR will be shown how to test their urine with dipsticks. They will be asked to check their urine every week and to contact the trial team if “+++” or “++++” are visible on 2 consecutive days. This is purely an aid to help patients identify a relapse, and dipstick monitoring will not be recorded as part of the trial documentation. Patients in PR will not test their urine, as dipsticks are not able to detect relapse in this situation.

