#### 13.4.2 Assessment of causality

- Definitely: A causal relationship is clinically/biologically certain. **This is therefore an Adverse Reaction**
- Probable: A causal relationship is clinically / biologically highly plausible and there is a plausible time sequence between onset of the AE and administration of the IMP and there is a reasonable response on withdrawal. **This is therefore an Adverse Reaction.**
- Possible: A causal relationship is clinically / biologically plausible and there is a plausible time sequence between onset of the AE and administration of the IMP. **This is therefore an Adverse Reaction.**
- Unlikely: A causal relation is improbable and another documented cause of the AE is most plausible. **This is therefore an Adverse Event.**
- Unrelated: A causal relationship can be definitely excluded and another documented cause of the AE is most plausible. **This is therefore an Adverse Event.**

Unlikely and Unrelated causalities are considered NOT to be trial drug related.

Definitely, Probable and Possible causalities are considered to be trial drug related.

A pre-existing condition must not be recorded as an AE or reported as an SAE unless the condition worsens during the trial and meets the criteria for reporting or recording in the appropriate section of the CRF.

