#### *16.1.4 Safety analysis*

The safety analyses will be based on the safety population. All safety parameters will be summarised. Summary tables will be presented for incidence rates (number of patients with at least one incidence) of, AESIs, and SAEs.

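### The hypogammaglobulinaemia AESI ignores nephrotic state, so low IgG caused by relapse may attenuate a rituximab excess in the pooled count

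*Protocol*

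**What the plan says.** Section 13.3.3 defines the event by absolute values: "Hypogammaglobulinaemia (IgG <400 mg/dL (Grade 3) and <250 mg/dL (Grade 4". It stands under a sub-heading that attributes it to rituximab, although the sentence introducing the whole list says only that a relation is possible. Section 13.2 repeats the item as an adverse reaction. No baseline, change from baseline or nephrotic state enters the definition. In the same list another item does set disease apart from drug: "Weight gain > 10% (not attributed to oedema".

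Section 13.3.2 makes a laboratory value reportable once it meets the definition: "Abnormal laboratory test results will not be recorded and/or reported as AEs unless they meet the criteria for SAE or AESI".

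The table in section 11.15 schedules IgG at eligibility, at remission, 6-monthly in remission, at month 24 and at relapse. Section 11.11 confirms the last of these: assessments at the relapse visit "will be identical to post-remission visit as well as a check for immunoglobulins G and M". Section 8.6.1 defines relapse as recurrent nephrotic syndrome, with albumin below 35 g/l and PCR above 300 mg/mmol. The relapse procedures in the synopsis do not list immunoglobulins.

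Section 16.1.4 sets the summary: "Summary tables will be presented for incidence rates (number of patients with at least one incidence) of, AESIs, and SAEs". Section 13.4.2 contains a partial safeguard: "A pre-existing condition must not be recorded as an AE or reported as an SAE unless the condition worsens during the trial".

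**The concern.** The relapse sample is an additional IgG measurement that only relapsing patients have, taken while plasma protein is being lost in the urine. A value below 400 mg/dL at that visit meets the definition whatever its cause, and one such value is enough for the patient to be counted. The trial is designed on the expectation that placebo patients relapse sooner and more often, so an effective drug would move disease-caused events towards the placebo arm.

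At stake is how the arm comparison can be read for the only laboratory-defined AESI that the protocol attributes to rituximab. A pooled count mixes a drug effect with a consequence of the primary outcome.

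**Working it through.** **Inputs**
- Median remission of 9 and 18 months, hazard ratio 0.50, 78 remitters, 67 events, uniform accrual over 30 months plus 24 months of follow-up: section 16.2 and Appendix 5.
- Remission rate 75%: section 16.2, applied here to both arms.
- q, the share of relapse IgG samples below 400 mg/dL from urinary loss alone: not in the documents; assumed 0.05 to 0.5.
- r, the share of rituximab remitters with a drug-caused event: not in the documents; assumed 5% to 20%, with none on placebo.

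**1. The protocol's own figure.** Schoenfeld: 4 × (1.960 + 0.842)² / (ln 0.5)² = 65.4, so 66 events against the stated 67. This reproduces the design.

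**2. Relapse by arm over the planned follow-up.** With exponential relapse and follow-up uniform between 24 and 54 months, P = 1 − [2^(−24/m) − 2^(−54/m)] / (30 × ln 2 / m).
- Placebo, m = 9: 1 − (0.1575 − 0.0156) / 2.310 = 0.939
- Rituximab, m = 18: 1 − (0.3969 − 0.1250) / 1.155 = 0.765
- Relapses among 39 remitters per arm: 36.6 + 29.8 = 66.4, in line with 67.
- Gap: 17.4 points of remitters, and 17.4 × 0.75 = 13.0 points of all randomised. The scaling is apt because non-remitters have no scheduled IgG after eligibility.

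**3. Disease-caused placebo excess, all randomised: 0.130 × q**

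| q | 0.05 | 0.10 | 0.20 | 0.30 | 0.50 |
|---|---|---|---|---|---|
| points | 0.7 | 1.3 | 2.6 | 3.9 | 6.5 |

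**4. What happens to a true excess among remitters.** Taking drug and disease causes as independent, placebo incidence is 0.939q and rituximab incidence is 1 − (1 − r)(1 − 0.765q). The difference is r − 0.174q − 0.765rq. The middle term comes from unequal relapse. The last arises because a patient with both causes is counted once.

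| true r (points) | q = 0.05 | 0.10 | 0.20 | 0.30 | 0.50 | excess vanishes at q of about |
|---|---|---|---|---|---|---|
| 5 | 3.9 | 2.9 | 0.8 | −1.4 | −5.6 | 0.24 |
| 10 | 8.7 | 7.5 | 5.0 | 2.5 | −2.5 | 0.40 |
| 20 | 18.4 | 16.7 | 13.5 | 10.2 | 3.7 | 0.61 |

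**5. The opposing force.** Main-phase follow-up ends at relapse (section 11.12). Mean time from remission to relapse or end of follow-up is P × m / ln 2: 0.939 × 9 / 0.693 = 12.2 months on placebo and 0.765 × 18 / 0.693 = 19.9 months on rituximab. At one IgG check every 6 months that is about 12.2 / 6 = 2.0 against 19.9 / 6 = 3.3 checks in remission. Rituximab patients therefore have more opportunity to record at least one event. Steps 3 and 4 leave this out.

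**The case against.** The strongest objection is that the protocol nowhere says nephrosis takes IgG below 400 mg/dL, or how often. That stands: the mechanism is plausible, but q is assumed, and at small q the effect is trivial. If rituximab does not delay relapse there is no differential excess, only the dilution term.

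A reader might infer that a rituximab excess *is* masked. The documents do not support that. In most of the scenarios above the excess is only attenuated, and the longer observation on rituximab pushes the other way. A reader might also take the 24-month relapse-free probabilities in Appendix 5 (0.157 and 0.397), read 84% against 60% relapsed, and use a gap of 24 points among remitters. But follow-up runs to relapse or trial closure and safety is summarised in all dosed patients, so 17 points of remitters, or about 13 of all randomised, is the better figure.

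The safeguards help only in part. The pre-existing-condition rule covers IgG that is low at baseline; it does not clearly cover IgG that recovers in remission and falls again at relapse. Investigators judge causality for each event, but the count in section 16.1.4 applies no causality filter. Sections 9.4 and 11.13 also unblind the local investigator at relapse, so this sample may be judged with the arm known.

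Finally, the tables are descriptive, and a split by nephrotic state could sit in the statistical analysis plan, which is not at hand. That lowers the weight of the point. The definition, the relapse sample and the at-least-one count are nevertheless fixed in the protocol.

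**Conclusion.** The point holds as a possible bias of unknown net size. The pooled count combines drug-caused and nephrosis-caused low IgG. If rituximab works as the design assumes, the nephrotic component adds about 0.13q to the placebo arm as a share of all randomised: 1.3, 2.6 or 3.9 points at q = 0.1, 0.2 or 0.3. This rests on the protocol's medians and remission rate, exponential relapse, equal remission by arm, and an assumed q. Masking or reversal needs a q that is large relative to the true drug effect, and the unequal remission time works against it. This is a cheap improvement to how the event is reported; it does not make the safety assessment invalid.

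**What to change.** In sections 13.3.3 and 16.1.4, keep recording every IgG below the cut-off and keep the total count. Add a table by arm that separates events on samples taken while nephrotic (PCR above 300 mg/mmol and albumin below 35 g/l at the same visit) from all others. Give the number of IgG samples or the follow-up time as denominator, so that the unequal observation is visible too.

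Do not adjust for IgG at the remission visit. Under section 10.1.7 the first dose is given within 4 weeks of Day 0 and the second about two weeks later, while remission may come as late as week 16. That value is therefore commonly post-dose, and adjusting for it could remove part of the drug effect. If a baseline is wanted, use the pre-dose eligibility IgG, bearing in mind that patients enter the trial nephrotic.

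The synopsis relapse list, which omits immunoglobulins, should be reconciled with sections 11.11 and 11.15.

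The cost is a definition line and one extra table; PCR and albumin are already collected at these visits. The not-nephrotic comparison conditions on a post-randomisation state that differs by arm, so it should stand beside the total and not replace it.

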|                                                                     |                                                                                                                                                                                                                                  |
|---------------------------------------------------------------------|----------------------------------------------------------------------------------------------------------------------------------------------------------------------------------------------------------------------------------|
|                                                                     | Health Costs questionnaire (6 monthly only).
IMP dosing (week 26 only), immunoglobulins G and M (week 26 then 6 monthly) and serum/urine pregnancy test (if applicable; week 26 only).                                        |
| Procedures: Relapse (within 2 weeks after relapse indicated) | Weight, blood pressure, Haematology, Biochemical analysis, Urinary PCR, 24 hour urine collection for proteinuria, concomitant medications, AE assessments, Health status questionnaire: EQ-5D-5L, Prednisolone compliance/dosing |
| Procedures: End of Trial                                     | End of Trial visits are defined as per section 11.9.                                                                                                                                                                             |
| Procedures for safety monitoring during trial                | Serious adverse events (SAEs) and other adverse events related to steroids or rituximab will be regularly reviewed by Trial Management Group (TMG) and Independent Data Monitoring Committee (IDMC).                             |
| Criteria for withdrawal of participants                      | Failure to achieve complete or partial remission at 16 weeks will result in withdrawal from the trial with no further trial visits                                                                                               |

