### **13.5 Reporting SAEs/SARs**

Each PI needs to record all AEs in the medical notes and report all serious AEs to the CI and TURING trial team using the trial specific SAE form within 24 hours of knowledge of the event. However, SAEs related to the underlying disease, as indicated in Section 13.2.4, will be exempt from expedited SAE reporting. These events will be designated as Adverse Events of Special Interest and details will be collected in the CRFs.

The Chief Investigator (CI) is responsible for ensuring the assessment of all SAEs for expectedness and relatedness is completed and the onward notification of all SAEs to the Sponsor immediately but not more than 24 hours of site investigator awareness of the event. The sponsor has to keep detailed records of all SAEs reported to them by the trial team.

The CI is also responsible for prompt reporting of all SAEs findings to the competent authority (e.g. MHRA) of each concerned Member State if they could:

- adversely affect the health of participants,
- impact on the conduct of the trial,
- alter the risk to benefit ratio of the trial,
- alter the competent authority's authorisation to continue the trial in accordance with Directive 2001/20/EC.

The completed SAE form can be faxed or emailed. Details of where to report the SAE's can be found on the TURING SAE form and the front cover of the protocol.

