### **18.3 Independent Data Monitoring Committee (IDMC)**

The IDMC is independent of trial investigators and the central co-ordination team at Cambridge. The composition of the IDMC will be defined in the IDMC charter. The group will meet approximately every 6 months while patients are receiving trial treatment or until end of trial. The IDMC will review reports from the central co-ordination team at Cambridge and give advice on continuing recruitment. There are no formal stopping rules for efficacy.

During the trial, interim analyses of all serious adverse events (SAEs) will be provided regularly in strict confidence to the chairman of the independent DMC.

In light of these reports and any other information considered relevant, the IDMC will advise the TSC if, in their view, the randomised comparisons have provided both (i) "proof beyond

reasonable doubt” that for all, or some specific types of, patients rituximab is clearly indicated or clearly contraindicated; and (ii) evidence that might reasonably be expected to influence materially the patient management of many clinicians who are already aware of the results of other trials. The TSC can then decide whether the trial should be modified, or to seek additional data according to the IDMC recommendation. Unless this happens, the TSC, all investigators, trial participants and all trial staff (except those who provide the confidential analyses to the IDMC) will remain blind to any interim results until the end of the trial. If a decision is made to continue, the IDMC will advise on the frequency of future reviews of the data on the basis of accrual and event rates.

The IDMC will also monitor trial recruitment at 18 months after the enrolment of the first patient, the interim feasibility assessment.

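### The SAE exemption for hypovolaemia and fluid-overload admissions is justified by frequent hospitalisation but has no limit by seriousness, so an admission that proves fatal or life-threatening needs no 24-hour report

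*Protocol*

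**What the plan says.** Section 13.3.3 of the protocol lists, as one AESI group, "Hospital admissions – Only those related" to hypovolaemia, to fluid overload secondary to nephrotic syndrome, or to thromboembolic events (items D1 to D3). It explains that patients with nephrotic syndrome are often admitted because of their disease. It then says: "Hospital admissions related to hypovolaemia or fluid overload secondary to nephrotic syndrome, or to thromboembolic events, will be" exempt from expedited SAE reporting, and adds that "these events will be designated as Adverse Events of Special Interest and details will be collected in the CRFs".

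The section closes with two rules. The first is "Each Principal Investigator must report all AESIs to the CI using the CRF in a timely manner". The second sends any serious AESI through the SAE procedure, "unless the AESI is related to hypovolaemia or fluid overload secondary to nephrotic syndrome".

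Section 13.5 sets the general rule: all serious adverse events go to the chief investigator and the trial team on the SAE form within 24 hours. It then exempts SAEs related to the underlying disease from expedited reporting, citing a Section 13.2.4, and says: "These events will be designated as Adverse Events of Special Interest and details will be collected in the CRFs".

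On oversight, 18.3 says that "interim analyses of all serious adverse events (SAEs) will be provided regularly in strict confidence" to the IDMC chair.

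**The concern.** The reason and the rule do not match. Frequent admission is a reason not to treat each admission as an expedited SAE merely because it is an admission. It is no reason to remove an event that is also fatal, life-threatening or disabling. Section 13.1.4 lists those as separate criteria, and the exemption does not refer to them.

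At stake is the speed of reporting and who sees the event while the trial is running. Under 13.5 the site's SAE report is the step that leads to the chief investigator's assessment of relatedness and expectedness and to notification of the sponsor within 24 hours. Under 18.1 the Trial Management Group reviews SAEs. An exempt event has only the CRF page behind it. All participants are nephrotic at Day 0 (9.1), and the first two infusions fall within the following weeks (10.1.7), so exempt events can occur during exposure to the trial drug, when a prompt second look at causality is most useful.

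**Working it through.** No arithmetic applies; the check is a comparison of the texts.

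**1. The exemption statements side by side**

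| Place | What is exempt | Exempt from | Limit by seriousness criterion |
|---|---|---|---|
| 13.3.3, admissions sentence | Admissions for hypovolaemia, fluid overload or thromboembolic events | Expedited SAE reporting | None |
| 13.3.3, closing sentence | Serious AESIs related to hypovolaemia or fluid overload | The SAE procedure | None |
| 13.5 | SAEs related to the underlying disease, by reference to 13.2.4 | Expedited SAE reporting | None |

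**2. The criteria.** Section 13.1.4 gives six: death, threat to life, hospitalisation, disability, congenital anomaly and important medical event. The reason in 13.3.3 speaks to the third only.

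**3. A case followed through.** A participant is admitted with fluid overload secondary to nephrotic syndrome and dies.
- By 13.1.4 the event is serious on two counts, hospitalisation and death.
- By the general rule in 13.5 it is due on the SAE form within 24 hours.
- By the closing sentence of 13.3.3 and the exemption in 13.5, it is not.
- What remains is the AESI page of the CRF, for which 13.3.3 sets no time limit.

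**4. The route to the IDMC.** Section 18.3 promises analyses of all SAEs and excludes none. No section says how an event held only on the AESI page is carried into them. The synopsis promises Trial Management Group and IDMC review of SAEs and of other events related to steroids or rituximab. Disease-related admissions are not named there.

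**5. Internal consistency**
- Thromboembolic admissions are exempt in the admissions sentence of 13.3.3 but absent from the exception in its closing sentence. A serious thromboembolic admission is therefore exempt under one and reportable under the other.
- Section 13.2.4, on which the exemption in 13.5 rests, does not exist. The listed admissions are in 13.3.3.
- For SAE reporting, 13.3.3 and 13.4.4 refer to 13.4, whereas 13.3.1 refers to 13.5, which is where the procedure stands.

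**6. What still applies to exempt events.** Section 13.6 keeps unexpected serious suspected reactions under expedited reporting with no exemption, and 16.1.4 tabulates both AESIs and SAEs in the safety analysis.

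**The case against.** The strongest reply is that the exemption is deliberate and narrow. It concerns disease-related events, its reason is stated, and 13.3.1 explains that excessive reporting would detract from the trial. The exempt items are listed as hospital admissions, so a death without admission is not clearly covered and the 24-hour rule would apply to it. Suspected unexpected reactions are still expedited, and the data are collected. All of this stands and limits the point. It does not supply the missing limit for an admission that proves fatal or life-threatening. The protection in 13.6 is also partial: it operates once someone suspects the trial drug, and attribution to nephrotic syndrome is what takes the event off the 24-hour form.

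A reader might infer four stronger conclusions, none of which the protocol supports.
- *The events bypass the IDMC.* The admissions sentence and 13.5 exempt them from expedited reporting, 13.5 still calls them SAEs, and 18.3 covers all SAEs. They would be lost only if the listings were built from SAE forms alone, which is nowhere stated.
- *They drop out of the SAE secondary outcome.* Seriousness is set by 13.1.4 and not by the form used, and 8.6.2 lists both SAEs and AESIs as outcomes.
- *The losses fall mainly in the placebo arm.* Both arms are nephrotic at Day 0. Non-remitters leave at week 16 (11.5.1), relapse ends main-phase follow-up apart from a window of up to 2 weeks (11.12), and open-label data do not enter the main safety assessment (10.2). Much of the exposure to these events is therefore before remission, and no direction of bias can be shown.
- *The primary endpoint is affected.* The outcome in 8.6.1 is relapse. Death from the disease appears in the state model of 16.1.2 and the censoring rule of 16.1.3, but nothing makes ascertainment depend on an expedited report.

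**Conclusion.** The point holds as a gap between the stated reason for the exemption and its wording. An admission for hypovolaemia or fluid overload that is fatal, life-threatening or disabling needs no 24-hour SAE form, and its route into the IDMC's interim analyses is not stated. The gap is in prompt reporting and interim oversight; it is not a loss of data from the final analysis.

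The protocol gives no expected number of such cases. Assuming 0 to 3 among 130 to 150 participants, the share is between 0 and about 2% (3/150 = 2.0%; 3/130 = 2.3%), and it may be none. For any case that does occur, the 24-hour report is wholly absent under the text as written. This assumes that sites follow 13.3.3 and 13.5 literally. The correction is worth making because it is cheap and each case would be a grave event in a blinded drug trial.

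**What to change.** - In 13.3.3 and 13.5, limit the exemption to listed admissions that are serious only because of hospitalisation. State that an event meeting any other criterion in 13.1.4 follows normal SAE reporting.
- Reconcile the two exemption sentences in 13.3.3 with each other and with 13.5, and say whether thromboembolic admissions are exempt.
- Correct the references: 13.5 should point to 13.3.3 in place of 13.2.4, and 13.3.3 and 13.4.4 should point to 13.5 for SAE reporting.
- In 18.3, state that exempt admissions recorded on the CRF are included by arm in the IDMC's safety reports.

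The cost is a few sentences in an amendment, one table in the IDMC report template and a handful of extra SAE forms. Routine disease-related admissions stay exempt, so the aim of avoiding excessive reporting is kept.
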